### Randomisation

Participants will undergo 1:1 web-based randomisation via www.Sealedenvelope.com.

### Study arms

#### Standard care

Standard clinical follow-up at 1 month, 6 months and 12 months with a vascular specialist. This will include wound inspection, pain score (NRS-11) and pedal pulse palpation. A handheld Doppler waveform can be used to supplement the examination if this is standard clinical care at the site. If there is a limb deterioration, further imaging can be requested.

#### Intervention arm

Integrated standard clinical follow-up plus ultrasound surveillance at 1, 6 and 12 months with lower limb arterial Doppler scans performed in hospital, prior to specialist review. Scans will include ABPI, toe pressures and lower limb arterial duplex. It is anticipated that in future trials, one or more of these may be dropped.

Ultrasound results will be reported contemporaneously and those with a treated vessel restenosis of >50% or occlusion, a new inflow or outflow vessel stenosis of >50% or occlusion, an ankle pressure or toe pressure drop of ≥20 mm Hg or absolute pressure values for severe ischaemia (ABPI <0.4 or toe pressure <30 mm Hg)^8^ will be red flagged for clinician attention.

Antithrombotic therapy in both arms will be standardised to first line (aspirin 75 mg once daily and rivaroxaban 2.5 mg two times a day^9^) and second line (clopidogrel 75 mg once daily).^10^ If patients take full anticoagulation for another indication, this should continue, and initiation of additional antiplatelet therapy will be at the operator’s discretion. All patients will require therapy with either high-dose statin therapy (eg, atorvastatin 80 mg) or ezetimibe.^11^ All patients will be offered nicotine replacement therapy.

Reinterventions will be discussed in a local vascular multidisciplinary meeting considering patient wishes, fitness, complexity of procedure and concomitant factors which add to amputation risk (microvascular disease, deformity and infection).

### Sample size

This is a hypothesis-generating feasibility study. A sample size of 70 (35 in each group) will allow us to estimate a 0.85 SD difference in the outcome measures between the groups (90% power, 5% significance and two-tailed). We have accounted for a 15% attrition rate over 12 months from all-cause mortality (12%) and for other reasons (3%). This leaves us with 30 patients per group for analysis of outcomes, which is recommended for a feasibility study with a parallel group design.

### Data monitoring

An independent trial steering committee has been appointed to oversee trial conduct. No data monitoring committee is planned, as this is a feasibility study. A trial management committee will oversee the delivery of the trial. Anglia Ruskin Clinical Trials Unit (ARCTU) will be the coordinating centre. ARCTU will work with the clinical investigators and trial manager on the delivery of the data management in compliance with the applicable regulations.

### Data analysis

As this is a feasibility study, data analysis will be descriptive. A screening log will be used to calculate eligibility rates and participation rates. Withdrawal rates will also be captured. The trial will be reported in accordance with the Consolidated Standards of Reporting Trials guidelines for feasibility trials.^12^

Questionnaire-based outcomes, including EQ-5D-L and VASCUQOL-6,^13^ will be analysed using mixed-effects models for repeated measures with terms for baseline, age, sex, site, intervention group, time (baseline, 1, 6 and 12 months) and an interaction of group and time. Adjusted means and group differences will be presented with 95% CIs. The data will be analysed using an intention-to-treat basis.

For secondary outcomes based on core reporting standards, such as amputation-free survival and limb salvage, the Kaplan-Meier survival curves with 95% CI will be used to present the data by two groups. Event rates will be recorded.

A summary of outcome measures will be described for subgroups of interest, such as gender, ethnicity and recruiting site.

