### Secondary outcomes

The secondary objective is to provide pilot data for a subsequent trial of clinical effectiveness. For these purposes, secondary outcomes based on core reporting standards will be recorded. These will be measured at 13 months to allow for any reinterventions and their effects triggered from the 12-month visit to be captured. Secondary outcomes are:

Limb salvage (freedom from above-ankle amputation).Amputation-free survival.Reasons for major amputation.Serious reintervention complications (unplanned intervention, critical care admission or death).Major adverse cardiac or cerebrovascular events.Mortality and cause of death.

Questionnaire-based secondary outcomes will be self-reported by questionnaire at baseline, 1-month, 6-month and 12-month clinic visits.

Quality of life (European Quality of Life-five dimensions level (EQ-5D-L).Disease-specific quality of life (Vascular Quality of Life Questionnaire-6 (VASCUQOL-6)).Independence in activities of daily living (Barthel Index).Pain scores (Numeric Rating Scale-11 (NRS-11)).

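### The questionnaire model uses baseline both as a covariate and as an outcome time, which makes the adjusted group differences look more precise than they are

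*Protocol article*

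**What the plan says.** The protocol article, Data analysis, states that the questionnaire outcomes "will be analysed using mixed-effects models for repeated measures". Baseline enters that model twice, because the article gives its contents as follows: "terms for baseline, age, sex, site, intervention group, time (baseline, 1, 6 and 12 months) and an interaction of group and time". The section then promises that "Adjusted means and group differences will be presented with 95% CIs".

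The Secondary outcomes section confirms that the four time levels are real assessments: the questionnaires are "self-reported by questionnaire at baseline, 1-month, 6-month and 12-month clinic visits".

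The article does not say that baseline rows are left out of the outcome. It names no covariance structure and does not say which contrast is meant by a group difference.

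**The concern.** A time level exists in a repeated-measures model only if there are outcome rows at that time. Read as written, each patient's baseline score is a response in one row and a covariate in all four. In the baseline row the covariate predicts the response perfectly if its coefficient is 1. In the follow-up rows the right coefficient is the baseline-to-follow-up correlation (for equal SDs), which is below 1. The model has one common coefficient for both.

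At stake is the precision attached to the adjusted questionnaire differences. The article's secondary objective is to supply pilot information for a later effectiveness trial. For outcomes of this kind in a small trial, the width of the interval is most of what is learnt.

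**Working it through.** **Inputs from the article (Sample size).** "A sample size of 70 (35 in each group"), to detect a "0.85 SD difference in the outcome measures between the groups (90% power, 5% significance and two-tailed"), with a "15% attrition rate over 12 months from all-cause mortality (12%) and for other reasons (3"%). The text adds: "This leaves us with 30 patients per group for analysis of outcomes".

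**The plan's own figure.** Per arm, n = 2(1.960 + 1.282)² / 0.85² = 29.1, so 30. After attrition, 35 × 0.85 = 29.75, about 30. The stated size is reproduced, and this point does not touch it. I use n = 30 per arm below.

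**Assumptions, not in the article.** Unit SD at each visit, exchangeable correlation ρ between visits, complete data, no true effect; age, sex and site omitted.

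**1. Random intercept, large-sample algebra.** The baseline covariate is constant within a patient, so its coefficient is estimated from patient means.

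- Coefficient as written (four rows, one of which is baseline itself): m = (1 + 3ρ)/4. With outcome rows at 1, 6 and 12 months only, it is ρ.
- Within-patient residual variance: 1 − ρ in both models.
- Between-patient variance: ρ − m² as written, ρ − ρ² with three outcome times.
- Model SE of the 12-month difference: √[(2/n)(1 − m²)] as written.
- True SD of that estimate: √[(2/n)(1 − ρ² + (m − ρ)²)].

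At ρ = 0.5: m = 2.5/4 = 0.625 against 0.50. Between-patient variance is 0.5 − 0.391 = 0.109 against 0.25. Residual variance is 0.5 in both. Model SE = √(0.0667 × 0.609) = 0.202; true SD = √(0.0667 × 0.766) = 0.226; ratio 0.89. With three outcome times, SE = √(0.0667 × 0.75) = 0.224.

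| ρ | slope m (should be ρ) | model SE | true SD | ratio | approx. coverage, 2Φ(1.96 × ratio) − 1 |
|---|---|---|---|---|---|
| 0.3 | 0.475 | 0.227 | 0.250 | 0.91 | 92.5% |
| 0.5 | 0.625 | 0.202 | 0.226 | 0.89 | 92.0% |
| 0.7 | 0.775 | 0.163 | 0.185 | 0.88 | 91.5% |

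**2. Simulation (REML, random intercept, exchangeable correlation).**

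- 30 per arm, complete data, ρ = 0.5: mean SE 0.202 against empirical SD 0.228 (ratio 0.89), coverage about 92%. With three outcome times: 0.224 against 0.226 (0.99), about 95%.
- The average over the follow-up visits fares worse: ratio 0.80, coverage about 88%, against 0.99 and about 95%.
- 35 per arm with 15% dropout: coverage of the 12-month difference 91.5%, 90.9% and 89.9% at ρ = 0.3, 0.5 and 0.7, against 94.3 to 94.5% with baseline as covariate only. The SE is 10 to 14% below the empirical SD.

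**3. The contrast that survives.** Under a random intercept the 12-month-minus-baseline group contrast has SE √[(2/n) × 2(1 − ρ)]. This uses only the residual variance, which is unchanged, and the covariate cancels. At ρ = 0.5 it is √(0.0667 × 1.0) = 0.258; simulation gave 0.2575 against an empirical SD of 0.2578, coverage about 95%, the same as without the covariate.

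**4. Unstructured covariance.** The baseline residual is (1 − b) times the centred baseline score, where b is the coefficient. The follow-up rows given baseline fit equally well for any b, so with 60 patients log L = constant − 60 ln(1 − b), which grows without limit as b approaches 1. In one simulated data set log L was −78.3 at b = 0; at b = 0.5 the formula gives −78.3 + 60 × 0.693 = −36.7, as computed. It reached 198 at 0.99 and 751 at 0.999999, while the baseline residual variance fell from 1.21 to about 1e-12.

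**5. Decaying (autoregressive) correlation, random intercept fitted.** Coverage of the 12-month difference over correlations 0.3 to 0.85 was 85 to 93% as written and 90 to 95% with three outcome times. At 0.85 it was 84.6% against 89.8%, so about half of the shortfall from 95% comes from the wrong covariance and stays.

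**The case against.** The strongest reply is that the harm depends on a covariance structure and a contrast that a journal article may leave to the full protocol or analysis plan. That is right as far as it goes. If only the change-from-baseline interaction under a random intercept were reported, the double use would cost nothing. An unstructured fit would probably fail visibly rather than give a plausible wrong answer. The bracket after time might also be only a list of the visits. But the article does fix the model terms and writes baseline into both places, and it promises adjusted means and group differences rather than the interaction alone. The objection narrows the consequence; it does not make the specification sound.

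Four stronger readings are tempting and should be resisted.

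- *The double use shrinks the residual variance.* It does not: within-patient variance was about 0.50 under both models at ρ = 0.5. The between-patient variance falls.
- *The next trial will be sized too small.* Nothing in the article says that this model's variance will size anything, and raw SDs would be unaffected.
- *Coverage falls to about 84 or 85% because of this error.* That happens only with decaying correlation and a random intercept, and part of it remains after correction.
- *False-positive conclusions follow.* The article calls its analysis descriptive and plans intervals, with no test or decision on these outcomes.

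**Conclusion.** The specification is wrong as written. Under a random intercept, the between-patient variance is understated, the SE of the 12-month adjusted difference is about 9 to 14% too small, and 95% intervals cover about 90 to 93%. Under an unstructured covariance the model cannot be properly fitted. These sizes rest on assumed exchangeable correlations of 0.3 to 0.7 and 30 to 35 patients per arm; in every correlation setting tried, the 12-month difference was covered less often as written than with three outcome times. Point estimates were essentially unbiased (at most about 0.012 SD, and the same after correction).

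The severity is moderate. The affected results are secondary questionnaire estimates in a feasibility trial. Attendance, completion and reintervention percentages do not come from this model.

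**What to change.** Use baseline once, in one of two ways:

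- (a) keep baseline as a covariate and let the outcome times be 1, 6 and 12 months only; or
- (b) keep all four times as outcomes, drop the baseline covariate, and constrain the two arms to a common baseline mean.

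State the choice in one sentence before analysis. If a separate analysis plan already makes it, reconcile the article's wording with that plan. Neither option repairs undercoverage from a misspecified covariance, so that structure needs its own justification.

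The cost is one sentence and no change to data collection. The intervals for the 12-month difference become somewhat wider: the SE ratio √[(1 − ρ²)/(1 − m²)] is 1.08, 1.11 and 1.13 at ρ = 0.3, 0.5 and 0.7.

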## Introduction

 Approximately 4000 people in the UK undergo major lower limb amputation each year due to peripheral arterial disease.^1^ The end stage, chronic limb-threatening ischaemia (CLTI), is characterised by nocturnal foot pain, ulceration and gangrene. If untreated, CLTI progresses to amputation, sepsis and death. Hence, CLTI has been the focus of a UK initiative, which aims to reduce amputation rates by expediting limb salvage interventions.^2^ Amputation can have secondary psychosocial impacts, including social isolation, frustration, anxiety and depression.^3^ The average cost of a major amputation, including inpatient care, rehabilitation and prosthetics, is £15 000.^4^ Additionally, amputees may need to move house, require community care, home and vehicle adaptations or Personal Independence Payments and lose employment opportunities.

Endovascular therapy has become the primary modality of limb salvage in CLTI, with >17 000 procedures performed annually in the UK.^1^ These include angioplasty, stenting and advanced interventions, such as intravascular lithotripsy or drug delivery via balloons or stents. These procedures are successful in over 90% of cases, but over 2 years, half of the target vessels restenose or reocclude, putting limbs at risk again.^5^

A recent meta-analysis examined amputation rates following endovascular therapy.^6^ It revealed that 10% of patients lose their leg within the first year of treatment. Restenosis rates were reported at 33% after 1 year and 46% after 2 years. Despite this, reintervention rates were relatively low: 10% at 1 year and 25% at 2 years. This suggests potential for more reintervention to prevent amputations.

Currently, UK vascular specialists detect restenosis through worsening pain, non-healing wounds or loss of previously palpable foot pulses. Out of 51 UK specialists surveyed for duplex ultrasound after endo revascularisation (DUSTER), 83% used clinical follow-up alone. In contrast, the 2019 European Society for Vascular Surgery guidelines recommend three lower limb Doppler scans within the first year post-treatment, combined with ankle-brachial pressure index (ABPI) and toe pressure measurements, in addition to standard clinical follow-up.^7^

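### The Kaplan-Meier limb-salvage curve censors deaths, so one minus the curve slightly overstates the proportion of patients amputated (at most about 10.7% against 10.0% at the protocol's own rates, under constant hazards)

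*Protocol article*

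**What the plan says.** The Secondary outcomes section lists "Limb salvage (freedom from above-ankle amputation" as its own endpoint, apart from amputation-free survival and from mortality. It sets the time point: "These will be measured at 13 months to allow for any reinterventions". It also says that these outcomes are to serve as pilot data for a later effectiveness trial.

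The Data analysis section assigns one method to both limb endpoints: "such as amputation-free survival and limb salvage, the Kaplan-Meier survival curves with 95% CI will be used to present the data by two groups". It adds that event rates are also to be recorded, without giving their form, and it describes the analysis as descriptive. It mentions neither cumulative incidence nor competing events.

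Two other places give rates. The Introduction reports from a cited meta-analysis: "It revealed that 10% of patients lose their leg within the first year of treatment". The Sample size section allows for 12% all-cause mortality and 3% other losses over 12 months.

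**The concern.** The two endpoints need different handling of death. In amputation-free survival a death is an event, and Kaplan-Meier estimates the right quantity. In limb salvage, as defined here, a death is not an event. The protocol does not say in words that deaths are censored, but a Kaplan-Meier curve for an endpoint that leaves death out can do nothing else. Censoring treats a patient who has died as still able to lose the limb at the rate seen in survivors. One minus the curve is then never below the proportion of patients amputated, and exceeds it whenever amputations follow deaths.

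At stake is the amputation risk that a planner of the later trial might read off the curve. The error is systematic, so a larger sample would not remove it.

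**Working it through.** **Plan's own figure.** The protocol gives no figure for the limb-salvage curve. The arm size used below does reproduce: for 0.85 SD at 90% power and 5% two-sided, n = 2 × (1.960 + 1.282)² / 0.85² = 29.1, that is 30 per group, and 35 × 0.85 = 29.75 after 15% attrition.

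**Inputs**
- Amputation by 12 months: 10% (Introduction).
- Death by 12 months: 12% (Sample size), taken here as wholly death without prior amputation.
- Time point: 13 months (Secondary outcomes).
- 35 patients per arm (Sample size).
- Assumption of this check: constant cause-specific hazards.

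**12 months**
- Total hazard: H = −ln(1 − 0.10 − 0.12) = 0.2485.
- Amputation hazard: 0.2485 × 10/22 = 0.1129. Death hazard: 0.2485 × 12/22 = 0.1355.
- One minus Kaplan-Meier: 1 − exp(−0.1129) = 10.7%.
- Cumulative incidence: 10.0% by construction. Excess: 0.7 points, about 7% relative.

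**13 months** (T = 13/12)
- One minus Kaplan-Meier: 1 − exp(−0.1129 × 13/12) = 11.5%.
- Cumulative incidence: (10/22) × [1 − exp(−0.2485 × 13/12)] = 10.7%.
- Excess: 0.8 points, or 35 × 0.0079 = 0.28 of a patient per arm. A simulation of 20,000 arms of 35 gave 11.6% against 10.8%.

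**Range**

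| Assumption | Excess |
|---|---|
| 10% amputation, only 6% competing death, 12 months | 0.3 points |
| 10% is itself a Kaplan-Meier figure (cumulative incidence 9.4%), 12 months | 0.6 points |
| All 12% die before any amputation (0.10/0.88 = 11.4%), 12 months | 1.4 points |
| 10% amputation, 20% death, 13 months | 1.4 points |
| 20% amputation, 20% death, 13 months | 2.9 points |

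The third row drops constant hazards and is the extreme of timing. The last two use rates that the protocol does not give.

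**Sampling error for comparison.** The 95% CI half-width for a 10% risk with 35 patients is 1.96 × √(0.10 × 0.90/35) = 9.9 points.

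**The case against.** The strongest reply is that the error has almost no practical weight. It is 0.7 to 0.8 points against a half-width of about 10, in a descriptive feasibility trial whose primary outcomes (attendance, completion, reintervention) and sample size are untouched. That stands, and it sets the priority.

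The inputs also lean high. The 12% is all-cause mortality and includes deaths after amputation, which do not compete. A reader might infer that competing death is as frequent as amputation here; the documents do not establish that.

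A reader might infer that these curves are the only pilot event rates. The Data analysis section provides separately for event rates, follow-up ends at 13 months, and only 3% is expected to be lost for reasons other than death. A crude proportion close to the cumulative incidence should therefore be obtainable, although the form of the recorded rates is not stated.

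A reader might also infer that the bias could create or hide a difference between arms. The figures do not support that in any useful size. With 10% true amputation in both arms and an assumed mortality of 6% against 18%, the same formula gives 1 − exp(0.625 × ln 0.84) = 10.3% and 1 − exp((10/28) × ln 0.72) = 11.1%, an artefact of about 0.75 points from a threefold mortality contrast. Cumulative incidence moves with mortality too: with an amputation hazard of 0.113 in both arms and death hazards of 0.06 and 0.20, Kaplan-Meier is equal (10.7%) while cumulative incidence is 10.4% and 9.7%.

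Finally, censoring at death is a recognised choice when the question is the rate of limb loss among patients still alive, and the protocol does not say that one minus the curve will be reported as the proportion amputated. That is fair. But for absolute risk, the quantity of interest in pilot event rates, the curve is the wrong source. The method is stated, so this is not a detail left to an unseen analysis plan.

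**Conclusion.** The point holds in a small form. The protocol names Kaplan-Meier for an endpoint that excludes death, so one minus the limb-salvage curve overstates the proportion amputated. At the protocol's own rates the excess is at most about 0.7 points at 12 months and 0.8 at 13 months. This rests on constant hazards, on all 12% mortality occurring without prior amputation, and on a 10% amputation rate taken from a meta-analysis rather than from this trial's population. Fewer competing deaths would make it smaller; deaths concentrated early could bring it to 1.4 points at 12 months. Amputation-free survival is not affected. The reason to act is the use of the secondary outcomes as pilot data; nothing here threatens the trial's conclusions.

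**What to change.** Low priority. In the Data analysis section, present major amputation by arm as an Aalen-Johansen cumulative incidence with death as a competing event and 95% CI. Keep Kaplan-Meier for amputation-free survival and overall survival. Show the Kaplan-Meier limb-salvage curve only as a supplement, for comparison with earlier literature. The cost is one sentence and a standard routine, with no new data and no change to the sample size.

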### Data management

Data will be written directly into the case report form (CRF) (source data) and then transcribed into the electronic CRF. Source documents will include original documents related to the trial, to medical treatment and to the history of the participant. Adequate source documentation will be maintained to allow reliable verification and validation of the trial data. CRFs will be in English.

The principal means of data collection from participant visits will be electronic data capture (EDC) in a bespoke database system via the internet. Data will be entered into the EDC system via site personnel. All source data recorded in the CRF will be signed by the investigator or his/her appropriate designee. All changes made following the electronic signing will have an electronic audit trail with a username and date. All trial documentation, including that held at participating sites and the trial coordinating centre, will be archived for a minimum of 10 years following the end of the study.

